#### 1. PPC

Will be diagnosed on a daily basis until hospital discharge using the diagnostic tool shown in Table 3. The data will be collected by an attending physiotherapist and phoned to a blinded assessor who determines the diagnosis of a PPC.

**Table 3 T3:** Postoperative pulmonary complication diagnostic tool

**During this trial the following criteria will be used to diagnose PPCs. Patients must be assessed before 11 am daily.**

**PPCs**
For the purposes of this study PPC will be diagnosed by presence of 4 or more of the following:
1. Chest radiograph report of atelectasis/consolidation. In the event of no CXR being taken, the CXR report from the previous postoperative day will be used. If neither are available a not available will be reported (n/a). If a CXR report is not available but a CXR has been taken a ward medical officer will be asked to report on this should this be the defining criteria for PPC.
2. An otherwise unexplained WCC of >11.2 × 10^9^/L *or *administration of respiratory antibiotics postoperatively (in addition to those administered routinely postoperatively). In the event of no WCC being taken, the WCC report from the previous postoperative day will be used. If none of these are available a n/a will be reported
3. Fever as seen by raised oral temperature >38°C with no focus outside of the lungs. The highest temperature within the previous 24 hours will be reported.
4. Positive signs of infection on sputum microbiology.
5. Production of purulent (yellow or green) sputum differing from preoperative status
6. SpO_2 _< 90% on room air (see measurement protocol below).
7. Diagnosis of pneumonia/chest infection by attending physician.
8. Re-admission to the ITU/HDU with problems which are respiratory in origin or a prolonged stay on the ITU/HDU (over 36 hours) with problems which are respiratory in origin.

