**Methods/Design:**

This single blind randomised controlled trial aims to recruit 184 patients following lung resection via open thoracotomy. All subjects will receive a preoperative physiotherapy information booklet and following surgery will be randomly allocated to a Treatment Group receiving postoperative physiotherapy or a Control Group receiving standard care nursing and medical interventions but no physiotherapy. The Treatment Group will receive a standardised daily physiotherapy programme to prevent respiratory and musculoskeletal complications. On discharge Treatment Group subjects will receive an exercise programme and exercise diary to complete. The primary outcome measure is the incidence of postoperative pulmonary complications, which will be determined on a daily basis whilst the patient is in hospital by a blinded assessor. Secondary outcome measures are the length of postoperative hospital stay, severity of pain, shoulder function as measured by the self-reported shoulder pain and disability index, and quality of life measured by the Medical Outcomes Study Short Form 36 v2 New Zealand standard version. Pain, shoulder function and quality of life will be measured at baseline, on discharge from hospital, one month and three months postoperatively. Additionally a subgroup of subjects will have measurement of shoulder range of movement and muscle strength by a blinded assessor.

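### An unreported chest film goes to a ward medical officer only when it would decide PPC status, and nothing stated masks that reader to the arm or the other items

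*Protocol article*

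**What the plan says.** - Status of the endpoint (Abstract, Methods/Design): "The primary outcome measure is the incidence of postoperative pulmonary complications", to be "determined on a daily basis whilst the patient is in hospital by a blinded assessor".
- Threshold (Table 3): "PPC will be diagnosed by presence of 4 or more of the following", with eight items listed.
- Criterion 1 (Table 3): "Chest radiograph report of atelectasis/consolidation". If no film was taken, the previous postoperative day's report is used, and if there is none the item is n/a. If a film was taken but not reported, "a ward medical officer will be asked to report on this should this be the defining criteria for PPC".
- Timing (Table 3): "Patients must be assessed before 11 am daily".
- Data flow (Outcome measurement, 1. PPC): "The data will be collected by an attending physiotherapist" and is "phoned to a blinded assessor who determines the diagnosis of a PPC".
- Knowledge of allocation (Recruitment and randomisation): the ward physiotherapist is told the group. Ward doctors are not mentioned.
- Day-one check (Inclusion/exclusion criteria): a subject who already has a PPC before randomisation on postoperative day one is excluded.

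**The concern.** The rule makes the request for a reading depend on what the reading would do to the primary outcome. Anyone who knows the rule can tell from being asked that calling atelectasis or consolidation turns the subject into a PPC case. The reader is a member of the ward medical staff for whom no masking is stated.

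Whether a film shows atelectasis or consolidation involves judgement. If the reader leans one way and also knows or guesses the arm, the tie-breaking readings can differ between arms for reasons unrelated to the lungs. The blinded assessor downstream gives no protection, because the leaning is already in the item that is phoned through. Changing who collects the daily data would not remove the problem either, since it lies in the rule that selects the film and its reader.

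**Working it through.** The plan states no figure for this rule, so the check is mainly a reading of the passages. The arithmetic afterwards shows scale only.

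**Passages side by side**

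1. PPC needs at least 4 of 8 items, so the film decides the day's score only when exactly 3 other items are present. With 2 or fewer it cannot produce a PPC; with 4 or more it is not needed.
2. The ward reading is conditional on the film being decisive. A request therefore corresponds to a subject at 3 items.
3. The person described as blinded for PPC is the assessor who is phoned and applies the rule. The film reading reaches that person as an input; no section has the assessor view the film.
4. No section states that the ward medical officer is blind to allocation, to the other items or to the reason for the request. No section offsets the conditional request, for example with a masked reader or a reading of every unreported film.
5. Treatment subjects receive daily ward physiotherapy and Control subjects none (Interventions, b. Postoperative treatment). Ward doctors could therefore recognise the arm, but the document does not say that they do.

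**Scale at the design assumptions** (Sample size: 20% Control, 5% Treatment, 84 per group)

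- Expected events: 0.20 × 84 = 16.8 in Control and 0.05 × 84 = 4.2 in Treatment.
- One reclassified subject: 1/84 = 1.19 percentage points in that arm.
- Single-event sensitivity (uncorrected chi-squared, 84 per arm): 13 v 5 events gives χ² = 3.98, p = 0.046; 13 v 6 gives χ² = 2.91, p = 0.088. Near the boundary, one reading can change the conclusion.

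**Sensitivity to differential over-calling** (the amounts are assumptions; exact enumeration of the uncorrected chi-squared test, two-sided 0.05, 84 per arm)

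| Over-calling in one arm only | Type I error: true rate 10% in both arms, Control over-called | Power: 20% v 5%, Treatment over-called |
|---|---|---|
| 0 points | 5.0% | 87% |
| 1 point | 5.5% | 80% |
| 2 points | 6.9% | 71% |
| 3 points | 9.2% | 62% |
| 5 points | 16.2% | 44% |

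A normal approximation gives similar values: type I error 5.5%, 7.0%, 9.3% and 16.4% for 1, 2, 3 and 5 points, and power falling from 84% to 70% at 2 points. Two points is 0.02 × 84 = 1.7 subjects in one arm. The document gives no count of unreported deciding films, so no row can be called the expected one.

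**The case against.** The strongest reply is that much of the alarm rests on inference, and a good part of that reply stands.

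- A reader might infer that the officer is told the film decides the endpoint. The text says only that the officer is asked to report on it. The officer *could infer* the consequence; being told is not supported.
- A reader might infer that the officer is unblinded. Only the ward physiotherapist is stated to know the group. Masking of the officer is not stated, and neither is knowledge of the arm.
- A reader might infer from the 11 am deadline that same-day films will often be unreported. The document gives no reporting times and no frequency.
- A reader might infer that asking selectively misclassifies subjects. It does not: films outside the three-item position cannot change the 4-of-8 result, and nothing stops their formal reports from being issued.
- A negative ward reading does not close the matter, because PPC is scored again each day to discharge.
- Clinical judgement enters elsewhere too, through the antibiotic part of criterion 2 and through criteria 7 and 8. The author of the formal radiology report is not stated to be blinded either.
- The rule has a purpose: it keeps a deciding item from being lost as n/a.

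These points limit the size and certainty of the concern. They do not remove it. Nothing in the text makes the formal report depend on the subject's score, whereas the ward reading is requested because of the score. That is avoidable, and the other sources of judgement are no reason to keep it. This is also not detail left to a fuller document, since the article states the conditional rule itself.

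**Conclusion.** The concern holds in a limited form. Criterion 1 allows the tie-breaking item of the primary outcome to be read by someone not stated to be blind to allocation or to the other items, who could infer the consequence. The blinded assessor cannot undo that reading.

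Differential bias needs two further conditions that the document does not establish: that the officer knows or guesses the arm, and that this influences the reading. The rule also acts only on films taken but unreported in subjects with exactly three other items. Its frequency, direction and size are therefore unknown. The figures above show that a few readings could matter with about 17 and 4 expected events; they do not show that the result will be biased. It would be tempting to say that four misread films in one arm would shift the difference by 4/84 = 4.8 points, about a third of the 15-point target. The four is an assumption with no source in the document and should not be quoted as an estimate.

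The change is worth making because the rule is unnecessary for an endpoint of PPC occurrence up to discharge and is almost free to replace.

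**What to change.** For outcome scoring after randomisation, replace the ward-medical-officer sentence in criterion 1 with a rule of this kind: where a film has been taken but not reported at the time of scoring, record the item as *report pending*; the blinded assessor completes that day's score from the formal radiology report when it is issued, dated to the day of the film.

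For the endpoint, only films that could decide PPC status need this follow-up, since the others cannot alter the score.

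Keep the day-one check before randomisation outside the change. That check decides exclusion and cannot wait for a pending report, and no allocation yet exists to bias the reading, so the ward reading may remain there.

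The cost is one sentence in Table 3 and a way of tracking pending items. Formal reports are already the source for criterion 1. Some PPC decisions will be finalised later than the day they refer to, and a film that is never formally reported stays n/a.

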***Sp0_***2 ***_measurement***
All SpO_2 _measurements will be taken in the morning prior to physiotherapy treatment. Prior to measurement of SpO_2_:
▪ The patient will be positioned in upright sitting (or long sitting if unable to be out of bed).
▪ O_2 _therapy will be withdrawn for a period of 5 minutes & SpO_2 _will be monitored but not recorded during this time. NB if patient on room air allow monitor to stabilise for 1 minute prior to reading.
▪ Measurement will be by designated pulse oximeter via a finger probe.
▪ After 5 minutes the SpO_2 _will be measured by reapplying the finger sensor to the index finger of one hand for 30 seconds.
▪ The lowest SpO_2 _during the 30 second measuring period will be recorded.
▪ If a patient's SpO_2 _drops below 88% at any stage of the measures they will be immediately returned to supplemental O_2 _as prescribed and measures abandoned. This will be noted and the value recorded.
▪ If the SpO_2 _drops below 90% (i.e. 89% or below) this will be noted as achieving as one of the criteria for PPC.
▪ Only patients with an SpO_2 _of 89% or below will not be taken off oxygen for SpO_2 _monitoring purposes (i.e. these patients will have already achieved criteria for PPC without removal from O_2_).
▪ If the physiotherapists notes the hands to be cool, peripheral shutdown, poor pulsatile flow on the SpO_2 _monitor or a dampened trace this will be recorded as being unreliable (N). A reliable trace will be recorded as (Y).

Key: CXR – Chest X Ray, SpO_2 _– Percutaneous oxygen saturation, PPC – postoperative pulmonary complication, WCC – white cell count, HDU – high dependency unit, ICU – intensive care unit.

#### 2. Length of Stay (LOS)

Length (number of days) of postoperative stay will be measured from data held on the hospital database.

#### 3. Shoulder function

Will be measured using the Shoulder Pain and Disability Index (SPADI) preoperatively, on discharge from hospital, one month and three months postoperatively. This is a self reported shoulder specific index developed by Roach et al. (1991) [26] which consists of 13 items in two subscales: pain (5 items) and disability (8 items). Each item is measured on an 11 point Likert scale where 0 = "no pain/no difficulty" and 11 = "worst imaginable pain/so difficult it required help" on each subscale respectively. The SPADI is scored by adding then averaging the two subscales to determine a score out of 100. A higher score means greater pain/disability. The SPADI has been demonstrated to detect change in subject's status over time, have good test-retest reliability, internal consistency and good criterion and construct validity although not within the thoracic surgical population [26-28].

#### 4. Shoulder ROM

In a subgroup of patients living within a 60 km radius of Auckland Hospital, active ROM will be measured preoperatively, on discharge from hospital, one month and three months postoperatively by a blinded assessor using digital inclinometry via a Plurimeter-V inclinometer. ROM will be measured in those muscle groups which are divided during surgery thus potentially affecting range of movement. The measures are:

a. Total shoulder flexion (the movement includes scapular motion)

b. Total shoulder elevation through abduction (the movement includes scapular motion)

c. Glenohumeral external rotation

All ROM measures (except external rotation) are taken with the subject fully upright in a standardised chair with the opposite forearm resting on a fixed table to eliminate trunk movement. Sitting has been chosen as the starting position for most measures due to the possibility of subjects with respiratory disorders being unable to tolerate supine lying. The position of the inclinometer is established by measurement from a clear surface marking (e.g. 1 cm above lateral epicondyle).

▪ Shoulder flexion is measured with the arm at the side, elbow extended, shoulder in neutral rotation with palm facing the thigh and thumb facing forwards. The subject actively flexes the arm with the thumb leading throughout, maintaining elbow extension.

▪ Shoulder elevation is measured with the arm at the side, elbow extended, arm in external rotation with the palm facing forward. The subject actively elevates the arm leading with the thumb maintaining elbow extension.

▪ Shoulder external rotation is measured in supine lying (on a standardised bed) with the arm at side, humerus supported by the bed, elbow flexed to 90°, forearm in the mid prone position, hand in fisted position, pointing towards the ceiling. The subject actively externally rotates the arm maintaining the elbow on the bed and leading with the dorsum of the hand.

For all movements care is taken to avoid trunk assisted movements. On each occasion the arm is returned to 0° and each movement is repeated twice after one practice measure. These measures, where possible, follow a standardised protocol that has been shown to have acceptable intra and interrater reliability for use within a randomised controlled trial [29]. As well as recording ROM subjects report maximum pain during each movement on a 0 – 10 verbal rating scale. The maximum reading for pain for each movement is recorded.

#### 5. Isometric muscle strength

In a subgroup of patients living within a 60 km radius of Auckland Hospital, muscle strength will be measured preoperatively, one month and three months postoperatively by a blinded assessor using a handheld manual muscle tester (Lafayette instruments) which has been shown to have moderate to high interrater and intrarater reliability [30]. Measurements will be made of those of muscle groups that have been divided during surgery and thus may affect muscle strength. The measures are:

a. Shoulder flexion

b. Shoulder abduction

c. Shoulder internal rotation

d. Shoulder extension

All measures are taken in the same position as described for ROM testing with the position of the dynamometer established in the same way using the easily identifiable surface markings of 1 cm above the elbow crease (for flexion), 1 cm above the lateral epicondyle (for abduction), 1 cm above the olecranon (for extension) or the skin crease (usually middle) between the radial styloid process and the head of the ulna (for internal rotation). The starting position is with the arm at the side with one gripped fist width between the distal end of the humerus and chest wall, the elbow flexed to 90° and the forearm in the mid prone position. This position was chosen due to the potential for subjects to be unable to commence muscle strength measures in 90° or 45° glenohumeral abduction as recommended by some authors [31,32]. Resistance is applied against the direction of shoulder movement for three to five seconds. The "make" (rather than "break") technique is used requiring the examiner to resist a maximal voluntary contraction by the subject which is essentially an isometric contraction and has been shown to have high interrater and intrarater reliability even in inexperienced examiners [33].

Standardised instructions and verbal encouragement is given and, after one practice contraction, each movement is measured three times with one minute between measures. Subjects report maximum pain during each movement on a 0 – 10 verbal rating scale. In keeping with other authors the maximum intensity of pain for each movement will be recorded [33-35].

#### Demographic and background information

Table 1 gives subject and operative data that will be collected and used to compare characteristics that could influence the outcome of the study. These data will be collected by the study investigators from subjects' medical records. In addition, records of any postoperative radiotherapy, chemotherapy and information regarding any additional shoulder treatments from health care professionals will be sought.

### Data analysis

Analyses will be conducted using an intention to treat principle for all randomised subjects. Demographic data will be analysed using descriptive statistics, Chi squared and Independent t tests or parametric equivalents.

A Chi squared test will be used to determine if there is any significant difference in the incidence of PPC between groups. LOS will be tested for normality of data. If normally distributed an Independent t test will be used to calculate the differences in mean LOS between groups and in differences in LOS in those subjects who do and do not develop PPCs. Data will be presented as mean differences with 95% confidence intervals. If data are not normally distributed a non parametric Mann Whitney U test will be used. The absolute risk reduction and number needed to treat will also be calculated for the primary outcome of PPC. Further between group comparisons for repeated measures of interval data (such as shoulder ROM, shoulder muscle strength, ADL and HRQoL) will be made using repeat measures ANOVA. Significant results will be analysed using post hoc tests such as the Scheffe F test. The alpha level for all statistical analyses will be set at 0.05.

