### Aims and Hypotheses

Thus the primary aims of the study are to:

1. Compare the incidence of PPCs between groups

2. Compare the postoperative length of hospital stay (LOS) between groups

The secondary aims are to:

3. Compare LOS in those subjects who develop PPCs and those who do not.

4. Compare the recovery of shoulder function, shoulder range of motion (ROM), and shoulder muscle strength (MMS) between groups

5. Compare the health related quality of life (HRQoL) between groups

The study hypothesis for the primary aims is:

H1. Routine postoperative prophylactic physiotherapy will significantly reduce the incidence of PPCs and LOS compared to no postoperative physiotherapy following open thoracotomy.

The hypothesis for the secondary aim is:

H2. A postoperative exercise programme will significantly improve the recovery of shoulder ROM, muscle strength and function following open thoracotomy.

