### Subjects

#### Inclusion/exclusion criteria

To be eligible for enrolment subjects must be adults admitted to Auckland City Hospital, New Zealand to undergo elective lung resection via open thoracotomy. They must understand written and spoken English and give informed written consent. Subjects will be excluded if they are unable or unwilling to comply with treatment, have tumour invasion into the chest wall or brachial plexus, present with a PPC prior to randomisation on postoperative day one, remain ventilated for longer than 24 hours following surgery or have received physiotherapy for shoulder problems or respiratory problems within two weeks prior to admission for surgery. Subjects with postoperative neurological or mobility complications requiring comprehensive physiotherapy input to progress towards discharge (defined as being more than two physiotherapy interventions), will be provided with the physiotherapy as required, remain in the group to which they were allocated and analysed using intention to treat principles. Subjects, who live within a 60 km radius of Auckland Hospital and can attend outpatient appointments, will form a subgroup that, in addition to all other measures, will attend for follow up shoulder ROM and muscle strength measures.

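### Comparing total stay by eventual PPC status is biased towards a longer stay in the PPC group, by an amount that depends on when PPCs occur

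*Protocol article*

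**What the plan says.** Under Aims and Hypotheses, secondary aim 3 is to "Compare LOS in those subjects who develop PPCs and those who do not". The Data analysis section assigns it the same independent t test as the between-arm LOS comparison ("in differences in LOS in those subjects who do and do not develop PPCs"), reported as a mean difference with a 95% confidence interval. The fallback is stated too: "If data are not normally distributed a non parametric Mann Whitney U test will be used". The alpha level is 0.05 for every analysis.

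Three other statements determine how the two groups form:
- **Start of risk.** Under Inclusion/exclusion criteria, patients who "present with a PPC prior to randomisation on postoperative day one" are excluded.
- **Detection window.** Under Outcome measurement, item 1, PPC "Will be diagnosed on a daily basis until hospital discharge using the diagnostic tool shown in Table 3".
- **Outcome.** Under item 2, "Length (number of days) of postoperative stay will be measured from data held on the hospital database".

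The article does not mention the day of PPC onset in this analysis, and it does not call the comparison descriptive.

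**The concern.** Group membership is settled during the period that the outcome measures. Everyone starts without a PPC, and the search for one stops at discharge, so a patient who leaves on day 4 cannot be labelled on day 7. Long-stay patients have more chances to enter the PPC group. Once they enter it, their whole stay counts there, including the days before onset. This is time-dependent (immortal-time) bias. The t test and the Mann-Whitney test share the same fixed grouping, so neither removes it, and a larger sample only makes a false result more certain.

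What is at stake is the answer to a listed aim. The reported difference would mix any real delay caused by PPC with this artefact, and the planned output could not separate them. A smaller point adds to it: one of the eight PPC items in Table 3 is itself partly a length of stay, namely a "prolonged stay on the ITU/HDU (over 36 hours) with problems which are respiratory in origin". Since four items are needed, that alone cannot make a PPC.

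**Working it through.** The article gives no figure for LOS by PPC status, so there is no stated number to reproduce. The check asks what the planned test returns when PPC has no effect on discharge.

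**Inputs from the article.** N = 184 (92 per arm). Planning PPC rates are 20% and 5%. Expected PPCs: 92 × 0.20 + 92 × 0.05 = 18.4 + 4.6 = 23, which is 23/184 = 12.5% overall. Risk starts after day 1 and ends at discharge.

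**Assumptions (not in the article).** LOS is log-normal in whole days, with median 6 or 7 and log-SD 0.3 to 0.5, drawn independently of PPC. PPC can first occur on day 2. Five timing patterns are used, each scaled to 12.5% PPC overall.

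**Mechanism in one formula.** With constant daily risk h, the chance of a PPC label given a stay of L days is 1 − (1 − h)^(L−1). For median 6 and log-SD 0.4, a 12.5% overall rate needs h = 0.0244. Then:
- L = 4: 1 − 0.9756^3 = 7.1%
- L = 10: 1 − 0.9756^9 = 19.9%

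The ten-day patient is 2.8 times as likely to be labelled, although PPC delays nobody.

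**Planned comparison under no effect, N = 184.** Each cell shows the mean LOS gap in days (PPC minus no PPC) and the Mann-Whitney rejection rate; nominal is 5%.

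| PPC timing | median 6, log-SD 0.4 | median 7, log-SD 0.5 | median 7, log-SD 0.3 |
|---|---|---|---|
| Constant daily risk | 1.38; 57.5% | 2.62; 75.0% | 0.84; 35.1% |
| Declining, 4-day scale | 0.61; 17.8% | 0.92; 23.3% | 0.34; 9.7% |
| Declining, 2-day scale | 0.30; 7.3% | 0.42; 5.7% | 0.14; 5.7% |
| First 3 risk days only | 0.15; 6.0% | 0.21; 6.0% | 0.02; 6.0% |
| First risk day only | 0.00; 3.8% | 0.00; 4.3% | 0.00; 4.8% |

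Under constant risk, with overall PPC rates from 5% to 20%, the gap runs from 0.83 to 2.71 days and Mann-Whitney rejection from 16.9% to 93.1%. The t test behaves similarly (20.5% to 92.2%).

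**Same constant-risk null data, PPC as a time-dependent state.** On each discharge day, count the n patients still in hospital, the n1 of them with a PPC by that day, and the D discharges. The expected number of discharges among PPC patients is D × n1/n. Sum observed minus expected over days, divide by the square root of the summed hypergeometric variance, and compare with 1.96. At 12.5% PPC the rejection rates, in the column order above, are 5.1%, 5.4% and 4.2%, with median discharge odds ratios of 1.01, 1.00 and 1.01. Across 5% to 20% PPC, rejection is 4.1% to 7.0%. So the fixed grouping produces the excess, and dating the PPC removes it.

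**The case against.** The strongest reply has four parts.

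1. **Size.** The article gives neither the LOS distribution nor PPC timing, so no figure above is a property of this trial. If nearly all PPCs arise in the first two or three days, the gap is a few tenths of a day at most and the test holds close to its nominal level. This stands. A reader might infer that aim 3 will show PPCs prolonging stay whatever the truth. The documents do not support that: even under constant risk, between a quarter and two thirds of the 12.5% simulations do not reject, and under early onset nearly all do not.

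2. **Intent.** Aim 3 says only that the groups will be compared. Neither H1 nor H2 covers it, and a raw difference is a valid description of how long each group stayed. This stands in part. The plan nevertheless attaches a test, a confidence interval and alpha 0.05, with no caveat, and the Background presents PPCs as contributing to longer stays. A causal reading is invited, though not stated.

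3. **Use.** A reader might expect the result to support a cost-saving argument. No cost outcome appears among the aims, outcomes or analyses. Cost is mentioned only in the Background, so that inference is not made here.

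4. **Proportion.** With about 23 PPCs expected, an elaborate multistate model would be ambitious for a non-randomised secondary aim. This stands, and it limits the fix.

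That a separate analysis plan may exist is no answer, because the article itself names the groups and the tests.

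**Conclusion.** The concern holds in direction and mechanism. The stated analysis for secondary aim 3 groups patients by an event that can be recorded only while they are in hospital, and so biases the LOS difference upward. Under the assumed log-normal LOS and no true effect, the bias runs from about 0 days, when PPCs precede the first discharges, to about 2.7 days under constant daily risk, where false positives range from 17% to 93%. Where this trial falls in that range cannot be settled from the article.

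The reach is limited. A reader might infer that the trial's main results are compromised. They are not: aims 1 and 2 compare PPC incidence and LOS between randomised arms, and this problem does not touch them, nor the sample size. The change should be made because aim 3 is formally tested and the planned output cannot show how large the bias is.

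**What to change.** Replace the ever/never test for aim 3 with one of two analyses that use the day of first PPC diagnosis, which the daily assessments already supply:

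- **Time-dependent state.** Analyse time to discharge, counting each patient as PPC-free until the day of diagnosis and as PPC from then on, with in-hospital death as a competing event.
- **Landmark.** Fix a postoperative day in advance. Among patients still in hospital on that day, compare remaining stay by PPC status at that day.

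With about 23 PPCs expected, keep the model simple and report the result as an observational association. If the raw ever/never difference is also shown, present it as a description, without a test or causal wording.

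The cost is a little more analysis work and no new data collection. The landmark option also drops patients discharged before the chosen day, and it counts patients whose PPC comes later as PPC-free.
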